#### Intervention group (post-implementation)

The intervention group consists of patients treated in one of the eleven cooperating regional hospitals diagnosed with any of the acute neurological diseases (stroke, seizures/status epilepticus, meningoencephalitis, and spinal cord injury) defined in inclusion criteria between November 2017 and July 2020.

#### Control group (pre-implementation)

Patients included in the control group were admitted and treated with one of the above mentioned acute neurological diseases in the same cooperating regional hospitals between November 2014 and May 2017, i.e. before start of the ANNOTeM implementation.

### Comparisons

#### Comparison of control and intervention period in cooperating regional hospitals

Patients with a diagnosis of a defined acute neurological disease and admitted to the cooperating regional hospitals during the intervention period from November 2017 to July 2020 are compared with patients of the same diagnosis group during the control period from November 2014 to May 2017 before the start of the intervention.

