#### Study time scale

Eligible patients who were admitted to the cooperating hospitals from November 16th 2014 to May 31st 2017 will form the control group. After an implementation period of the ANNOTeM concept, patient recruitment was started in November 2017 in the first intervention hospitals and will continue until July 2020 for primary analysis with 90 days’ follow-up (for details see Table 1). The same periods will be used for the evaluation of time trends in non-network hospitals.

**Table 1 Tab1:** Start of implementation and recruitment of patients as well as end of recruitment of the intervention hospitals in the study

Intervention hospitals	Start of implementation period	start of recruitment	end of recruitment
BER	10/04/2017	01/02/2018	07/31/2020
LUD	07/02/2017	11/16/2017	07/31/2020
NAU	07/08/2017	11/16/2017	07/31/2020
LUC	08/20/2017	11/18/2017	07/31/2020
KYR	12/11/2017	11/16/2018	07/31/2020
STR	12/23/2017	03/23/2018	07/31/2020
TEM	12/30/2017	03/30/2018	07/31/2020
RAT	10/06/2018	01/04/2019	07/31/2020
UEC	10/16/2018	01/14/2019	07/31/2020
GAR	11/12/2018	02/10/2019	07/31/2020
PRE	10/16/2018	01/14/2019	07/31/2020

An interim analysis without significance testing is planned after completion of 50% of patient follow-ups in order to inform decision makers about the progress of the scientific evaluation and options for transition into regular care; after the last follow-up is completed end of October 2020, the final analysis is expected in January 2021 (Fig. 2).

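### The primary intervention group is defined in two incompatible ways: one calendar window for all eleven hospitals, and hospital-specific recruitment starts in Table 1

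*Protocol article*

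**What the plan says.** Two sections of the protocol article use a single calendar window.

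- Intervention group (post-implementation): "The intervention group consists of patients treated in one of the eleven cooperating regional hospitals" with a qualifying diagnosis, as "defined in inclusion criteria between November 2017 and July 2020".
- Comparison of control and intervention period in cooperating regional hospitals, which sets out the pre/post contrast: patients "admitted to the cooperating regional hospitals during the intervention period from November 2017 to July 2020".

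The Study time scale section describes a staggered start. It begins "After an implementation period of the ANNOTeM concept", and goes on that "patient recruitment was started in November 2017 in the first intervention hospitals and will continue until July 2020 for primary analysis", with a pointer to Table 1. The table is captioned "Start of implementation and recruitment of patients as well as end of recruitment of the intervention hospitals in the study" and gives each hospital its own dates. Recruitment starts run from 16 November 2017 (LUD, NAU) to 10 February 2019 (GAR), and all hospitals end on 31 July 2020.

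For the comparator hospitals the same section says "The same periods will be used for the evaluation of time trends in non-network hospitals".

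The Primary analysis section states that the insurance data are anonymous, so the effect of a teleconsultation cannot be determined per patient and effects are evaluated in clusters.

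**The concern.** The two definitions select different primary populations. A GAR patient admitted in December 2017 is an intervention patient under the window wording, although implementation at GAR began only on 12 November 2018. Under Table 1 that patient is not.

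The choice carries more weight here than in most trials. Patients are identified from claims, so no enrolment step removes early admissions, and no patient-level marker of exposure is available. Hospital and admission date together are the exposure definition. If the window wording is applied, admissions before the intervention existed at a hospital count as exposed, and the contrast is pulled toward no effect.

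If Table 1 is applied, a second question opens. The non-network hospitals are there to separate the intervention from time trends, and this works only if their post-period covers the same calendar time as that of the network hospitals. The text does not say whether the staggered starts carry over to them. In an open-label study, neither choice should be left until data are seen.

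**Working it through.** **The plan's own figure.** The documents give no figure for the share of time before recruitment start. The related stated figure is at least 1820 per group for 80% power, with 39% versus 32% and two-sided alpha 5%. The two-proportion formula is n = [1.96·√(2p̄(1−p̄)) + 0.8416·√(p₁(1−p₁)+p₂(1−p₂))]² / (p₁−p₂)². With p̄ = 0.355 this gives (1.3264 + 0.5680)² / 0.0049, which rounds up to 733 per group (761 with continuity correction). So 1820 is not reproduced. On these inputs its power is Φ[(0.07·√1820 − 1.3264)/0.6749] = 99.3%. The figure may be the number of patients available, or it may contain an unstated design effect of about 1820/733 = 2.5. Both cases are carried through below.

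**Time before recruitment start.** Inputs are the Table 1 dates. The window runs from 16 November 2017 (the earliest recruitment start) to 31 July 2020, which is 989 days; 11 × 989 = 10,879 hospital-days.

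| Hospital | Days before recruitment start | of which before implementation | Share of window before recruitment start |
|---|---|---|---|
| LUD, NAU | 0 each | 0 | 0% |
| LUC | 2 | 0 | 0.2% |
| BER | 47 | 0 | 5% |
| STR | 127 | 37 | 13% |
| TEM | 134 | 44 | 14% |
| KYR | 365 | 25 | 37% |
| RAT | 414 | 324 | 42% |
| UEC, PRE | 424 each | 334 each | 43% |
| GAR | 451 | 361 | 46% |
| Sum, 11 hospitals | 2,388 | 1,459 | 22.0% |

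- Before recruitment start: 2,388/10,879 = 22.0% (23.1% if the window opens on 1 November 2017).
- Before any implementation: 1,459/10,879 = 13.4%.
- In the implementation phase: 2,388 − 1,459 = 929; 929/10,879 = 8.5%.
- Remaining under Table 1: 10,879 − 2,388 = 8,491, or 78%.

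**Dilution if the single window governs.** Assume equal case volume per hospital and no effect before recruitment start. The difference becomes 7 × (1 − 0.2195) = 5.46 points, that is 39% versus 33.5%. The number needed rises from 733 to 1,215 per group. Power at 1820 per group becomes Φ[(0.0546·√1820 − 1.3326)/0.6788] = 92.9%. If 1820 instead carries a design effect of about 2.5, the effective size is about 730 per group, and power falls from 80% to about 58%. These figures compare two proportions; they are not a power calculation for the Cox model at the multiplicity-adjusted alpha.

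**Calendar mismatch if Table 1 governs.** Let dᵢ be the days before recruitment start in hospital i, and assume equal daily admissions. The remaining time in hospital i is centred dᵢ/2 later than the full window. Weighting by the days remaining, the shift is Σ dᵢ(989 − dᵢ) / (2 × 8,491) = 1,457,860/16,982 = 86 days. This applies only if the comparators keep the full window.

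**Table 1 intervals.** From implementation start to recruitment start: 90 days in eight hospitals, 137 in LUD, 131 in NAU, 340 in KYR. With 90 days in KYR, the 22.0% would be (2,388 − 250)/10,879 = 19.7%.

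**The case against.** The strongest reply is that the window wording gives only outer bounds and Table 1 gives the operative dates. The Intervention group section is headed post-implementation, the Study time scale section ties the staggered recruitment to the primary analysis, and a patient admitted eleven months before local implementation is not post-implementation in any ordinary sense. This is a fair reading and may well be the intended one. On it, the share before recruitment start is 0%. What it does not remove is that the two sections that define the group and the contrast state one window for all hospitals, with no reference to Table 1.

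A reader might infer that 22% of the intervention group is unexposed. The documents do not support that, for three reasons. The figure depends on which definition governs. Only 13.4% precedes any implementation; in the other 8.5% exposure is partial or unknown. And it is hospital-time: case volumes are not given, so the patient share under the window wording could lie anywhere between the single-hospital extremes of 0% and 46%.

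A reader might also take the fall in power to about 58% as established. It rests on a design effect that the documents nowhere state; the stated inputs give 92.9%.

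The phrase about using the same periods for non-network hospitals follows directly on the reference to Table 1, and those hospitals were matched to the network. Hospital-specific comparator windows are therefore compatible with the text. The mismatch is a possible consequence of an open wording, not a stated plan.

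The 340 days at KYR contradict no stated rule, and two other hospitals also depart from 90 days. The row warrants a query but is not a demonstrated error.

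**Conclusion.** Wrong as written. The article gives two definitions of the primary intervention group that cannot both be applied, and it does not rank them. A condensed article may leave detail to the full protocol, but here both definitions are printed and they conflict.

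The size depends on the reading. Under the single window, 22.0% of intervention hospital-time comes before recruitment start, and the assumed effect loses about a fifth (7 to about 5.5 points), given equal volumes and no effect before recruitment start. The power cost ranges from modest to serious according to what 1820 contains. Under Table 1 there is no such dilution, but the comparator windows are unspecified, with a possible average offset of about 86 days that would weaken the control for time trends. The conflict itself rests on no assumption.

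**What to change.** - In the Intervention group section and in the section comparing control and intervention periods, count a patient as intervention only if admitted on or after that hospital's Table 1 recruitment start. State that admissions between November 2017 and that date are excluded from the primary comparison.
- In the section on non-participating hospitals and in Study time scale, give each matched non-network hospital the post-period window of its network counterpart.
- Check the KYR dates against site records, and correct or explain them.

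The cost is a hospital-specific date filter on the insurer data and some wording. The intervention group becomes smaller than the full window would give: 78% of hospital-days remain. The expected number per group should be checked against the window finally adopted. The control period need not change.

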#### Comparison with non-participating hospitals

In order to investigate whether differences in outcome in the cooperating hospitals may be caused by temporal trends, the composite primary outcome will also be analysed for the same two periods in patients fulfilling the identical inclusion criteria but being treated in hospitals of the same region that do not participate in the network (non-network community hospitals). The non-network hospitals were matched according to geographical location, size and amount of acute neurological cases per year. Data for this comparison are also provided by the three insurance companies.

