### Study design and setting

ANNOTeM is a multi-center, controlled, open-label, two-arm intervention study. Primary and secondary outcomes will be evaluated for pre- and post-implemention of the network. The ANNOTEM intervention started in November 2017 and is expected to run until the end of July 2020.

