#### Secondary outcomes

Secondary outcomes are: 1) Treatment proportions for evidence-based therapies such as Stroke Unit treatment, intravenous thrombolysis, endovascular thrombectomy, hemicraniectomy; 2) Hospital transfers; 3) Mortality (Cox regression); 4) Nursing home care; 5) Costs for acute inpatient treatment, hospital transfers, rehabilitation treatment and nursing care.

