### Statistical analyses

#### Primary analysis

Because health insurance data will be provided anonymously, we cannot determine the effect of telemedicine consultation on an individual patient level. Rather, we will evaluate the effects of the ANNOTeM concept in clusters. The primary outcome will be analysed as the time from the index visit to the occurrence of the compound outcome as described above. Separate Cox models will be fitted for eligible patients insured at the cooperating health insurance companies, admitted and treated in both, the pre-implementation period and the intervention period. Cox models will comprise sex (m/f only), age and co-morbidity (Y/N) as covariates. Hazard rate ratios will be used to compare time-to-compound event between the two periods. All tests will be performed at a significance level of alpha = 0.05, adjusted for two-sided testing and the k = 6 tests of the primary and secondary analysis. All tests will be performed using the statistics package ‘R’ (version 3.6).

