#### Secondary analysis

The secondary analysis compares the survival rates obtained in the primary for the network clinics with the group of non-cooperating hospitals using the log-rank-test for 2 × 2 factorial designs (control vs intervention period and network vs non-network hospitals). A treatment effect will be revealed by a significant interaction in favour of the network clinics during the intervention period.

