We acknowledge several limitations of the study: Changes in the care of patients with effects on the primary outcomes measured here may occur independently of study design through health policy measures and health care innovations. This can result in an overestimate of improved care for the intervention group compared to the pre-implementation control group. In order to control for this possible time trend, we have introduced a parallel control group of patients treated in non-network hospitals. A further limitation is that the definition of part of the composite outcome is based on routine data of the health insurances. It is possible that patients or their relatives do not apply for home care support provided by the health system even when they have a respective need of assistance. In addition, the decision for home care also depends, among other things, on the available social support at home or personal preferences. However, previous analyses have shown that the parameters of care support and home care correlate well with the degree of disability [18]. The approach taken in this project will be evaluated in the setting of the German health care system and results can therefore not be generalized.

On the other side, the study has several important strengths. First, the total number of patients treated in the hospitals with regard to the main diagnoses is recorded on the basis of health insurance data. Thus, the bias of patient selection by informed consent procedures often present in clinical studies is minimized. Second, study outcomes are assessed independently. Third, the combination of data collected within the telemedicine consultations along with quality management of the health insurance data provide the opportunity to evaluate the effects with a direct link to the health care context.

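### The non-network comparison is stated only for the composite outcome, so the secondary outcomes have no stated protection against the time trend that the protocol says can inflate benefit

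*Protocol article*

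**What the plan says.** Four places in the protocol article bear on this.

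- **Comparison with non-participating hospitals.** The purpose is stated as "In order to investigate whether differences in outcome in the cooperating hospitals may be caused by temporal trends", and the outcome named is the composite: "the composite primary outcome will also be analysed for the same two periods in patients fulfilling the identical inclusion criteria".
- **Secondary analysis.** The period by network interaction is defined on the same outcome: "The secondary analysis compares the survival rates obtained in the primary for the network clinics with the group of non-cooperating hospitals".
- **Study design and setting** and **Secondary outcomes.** The contrast given is "Primary and secondary outcomes will be evaluated for pre- and post-implemention of the network". The secondary outcomes begin with "Treatment proportions for evidence-based therapies such as Stroke Unit treatment, intravenous thrombolysis, endovascular thrombectomy, hemicraniectomy" and go on to hospital transfers, "3) Mortality (Cox regression); 4) Nursing home care" and costs.
- **Discussion (limitations).** Policy changes and innovations may alter care independently of the study. Of the before/after comparison it says: "This can result in an overestimate of improved care for the intervention group compared to the pre-implementation control group". The parallel non-network group is presented as the control for this.

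The adjustment described for the primary analysis has no term for calendar time or hospital group: "Cox models will comprise sex (m/f only), age and co-morbidity (Y/N) as covariates". The Sensitivity analysis section plans separate analyses of death, nursing home care and paid nursing care, and mentions no non-network contrast for them.

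**The concern.** The protocol identifies a source of bias, says which way it acts and names a remedy, then attaches the remedy to one outcome. The reasoning in the Discussion applies equally to mortality, nursing home care, use of acute therapies, transfers and costs. All of these can move between 2014–17 and 2017–20 for reasons unrelated to the network. If the text is followed as written, a change common to the whole region would appear in the network hospitals' before/after difference and could be reported as an effect of the intervention.

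The k = 6 multiplicity adjustment in the Primary analysis section does not help. It limits chance findings and leaves bias in the estimate untouched.

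**Working it through.** **Step 1: outcome by outcome, which control is stated?**

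| Outcome | Before/after in network hospitals | Non-network comparison stated |
|---|---|---|
| Composite (primary) | yes | yes |
| Mortality (Cox) | yes | no (only as part of the composite) |
| Nursing home care | yes | no (only as part of the composite) |
| Therapy proportions | yes | no |
| Transfers | yes | no |
| Costs | yes | no |

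Study time scale, the caption of Fig. 2 and the Discussion mention the parallel group in general terms. None of them attaches it to a secondary outcome.

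**Step 2: how large could the misattribution be?** The protocol gives no figure on this point, so there is none to reproduce. The inputs are:

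- n = 1820 per period, the number expected in the Sample size calculation. It is used here only as a head count. The standard two-proportion calculation for 39% against 32% at 80% power and two-sided 5% gives 733 per group. That mismatch is a separate matter.
- Two-sided alpha of 0.05 (z = 1.960), and 0.05/6 = 0.0083 (z = 2.638) if the k = 6 adjustment is Bonferroni. The method is not named.
- Event rates: **assumed**, with the whole change due to a regional trend and no network effect.
- Independent patients, so hospital clustering is ignored.

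With rates p₁ and p₂, mean p̄ and d = p₂ − p₁:

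- s₀ = √[2p̄(1−p̄)/n]
- s₁ = √{[p₁(1−p₁)+p₂(1−p₂)]/n}
- P(significant) = Φ[(−z·s₀−d)/s₁] + 1 − Φ[(z·s₀−d)/s₁]

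*Mortality, 20% to 18%.* s₀ = √(0.3078/1820) = 0.01300, s₁ = √(0.3076/1820) = 0.01300, d = −0.02.

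- At 0.05: Φ[(−0.02549+0.02)/0.01300] = Φ(−0.42) ≈ 0.337; the other tail is negligible.
- At 0.05/6: Φ[(−0.03431+0.02)/0.01300] = Φ(−1.10) = 0.136.

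*Thrombectomy, 2% to 3%.* s₀ = √(0.04875/1820) = 0.005176, s₁ = √(0.0487/1820) = 0.005173, d = 0.01.

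- At 0.05: 1 − Φ[(0.01014−0.01)/0.005173] = 1 − Φ(0.03) = 0.489.
- At 0.05/6: 1 − Φ[(0.01365−0.01)/0.005173] = 1 − Φ(0.71) = 0.240.

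Range over other assumed trends:

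| Assumed trend, no network effect | alpha 0.05 | alpha 0.05/6 |
|---|---|---|
| Mortality 15% to 14% | 14% | 4% |
| Mortality 15% to 13% | 41% | 18% |
| Mortality 20% to 18% | 34% | 14% |
| Mortality 20% to 17% | 65% | 38% |
| Thrombectomy 2% to 3% | 49% | 24% |
| Thrombectomy 4% to 6% | 79% | 55% |
| Thrombectomy 2% to 4% | 94% | 82% |

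If the trend is the same in both hospital groups, it cancels in the interaction and the error rate returns to 5% (0.83%).

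**Step 3: what does the interaction cost in precision?** With four groups of equal size (assumed; the non-network number is not given), its variance is about twice that of the before/after difference, so the standard error grows by √2 ≈ 1.41. For the 20%/18% case the 95% half-width goes from 1.96 × 0.0130 = 2.5 points to 1.96 × 0.0184 = 3.6 points.

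**The case against.** The best reply is that this is a condensed article. Naming the composite for the non-network comparison does not exclude other outcomes, and a full protocol or analysis plan could extend it. The before/after sentence covers primary and secondary outcomes alike. Since the composite is also compared with non-network hospitals, that sentence cannot by itself show that the secondary outcomes are before/after only. This stands as a limit on wording: the protocol states no control for these outcomes, but does not rule one out. It does not remove the point, because two sections fix the scope of the comparison and both fix it on the composite.

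A reader might infer more than the text supports:

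- *That the protocol expects a trend.* The Discussion calls it possible and speaks of effects on the primary outcomes.
- *That every secondary outcome is formally tested before/after.* A method is given for mortality alone, and the six tests are not listed. The probabilities above apply if such tests are run. The bias in the estimate is there either way.
- *That thrombectomy is the outcome most exposed.* The Background credits stroke units, thrombolysis and thrombectomy together and gives no trend in use.
- *That the secondary outcomes drive the decision on regular care.* Study time scale links decision makers to an interim analysis without significance testing and names no secondary outcome.

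It is also fair to say that mortality and nursing home care receive some indirect control as components of the composite. A composite result, however, does not show whether a change in one component is a network effect.

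**Conclusion.** The point holds in this form: the trend control that the protocol considers necessary is stated for the composite and for no secondary outcome, so a shared regional change in those outcomes could be taken for a network effect. It should be corrected, but it does not touch the primary outcome, which has its parallel comparison.

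The size depends on trends that the protocol does not give. For small assumed shifts of one to two percentage points, the chance of a significant before/after result without any network effect runs from 14% to 94% at 0.05, and from 4% to 82% at 0.05/6. The calculation treats mortality as a simple proportion, ignores clustering, and puts all diagnoses in the thrombectomy denominator although the therapy is for stroke. A cluster-aware test would reject less often, but the estimate would still be off by the full trend. The remedy in turn assumes that network and non-network hospitals share the trend.

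**What to change.** - **Mortality and nursing home care.** State that both are analysed with the same period (control/intervention) by hospital group (network/non-network) interaction as the composite, using Cox models. Both are components of the composite, so the data that the insurers supply for non-network patients must already identify them in some form. Confirm that the delivery includes the date of each component, including deaths after an earlier nursing-care event. The article does not say so.
- **Therapies, transfers and costs.** Apply the same interaction, with models suited to proportions and to costs, where the insurers' account data cover non-network patients.
- **Anything left before/after only.** Report it as descriptive, without a causal claim.

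The cost is analysis-plan wording, a few extra models and wider intervals (about 1.4 times with equal group sizes). Procedure and cost items for non-network patients may have to be added to the insurer delivery.
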